## Abstract

**Introduction::**

Pericoronitis is a common disease in the eruption phase of third molars, sometimes debilitating, with an impact on the quality of life. The most indicated treatment in the initial phase is the irrigation for cleanliness of the region. In order to reduce the chances of systemic dissemination of the infection and antibiotics use, it is mandatory to test effective treatments in the initial phase of pericoronitis avoiding the evolution of the infectious disease. Photodynamic therapy (PDT) is an interesting alternative because it is an effective antimicrobial treatment that is easy to perform and does not select bacterial resistance. The methylene blue (MB) used in PDT has been studied in an oral formulation, which optimizes the formation of monomers increasing its antimicrobial action.

**Objective::**

The aim of this study is to evaluate the effectiveness of PDT with MB in an astringent vehicle in pericoronitis on the initial phase in healthy patients through microbiological, clinical, and immune response. The impact of pericoronitis on oral health-related quality of life (OHRQoL) of these patients will also be evaluated.

**Method::**

In this randomized, controlled, double-blind clinical bioequivalence protocol, 64 healthy patients with pericoronitis will be evaluated. Patients will be randomized into the positive control group (G1) (n = 32): irrigation with sterile saline and PDT (conventional MB at 0.005% concentration and irradiation with low intensity laser λ = 660 nm, 9J per point and radiant exposure of 318 J/cm^2^), and the experimental group (G2) (n = 32): treatment identical to G1, however, MB will be delivered in a new formulation for oral use. Microbiological analysis will be performed by RT-PCR for the bacterium *Tannerella forsythia.* Gingival crevicular fluid and saliva will be collected to evaluate cytokines by Luminex assay (Luminex Corporation, Austin, TX). The pain (visual analogue scale), swelling and buccal opening (digital caliper), and OHRQoL will also be evaluated through the OHIP-14 questionnaire. The variables will be evaluated in T1 (baseline), T2 (immediately after PDT), and T3 (4th day after PDT). Registration: clinicaltrials.gov NCT 03576105. Registered in July 2018.

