## Methods

2

The protocol was approved by the Research Ethics Committee of Nove de Julho University (UNINOVE), number # 2.732.106 and registered at clinicaltrials.gov NCT 03576105. The study is in accordance with the Declaration of Helsinki (revised in Fortaleza, 2013).

Participants who accept to participate will sign the Informed written Consent Form after verbal and written explanation of the study. The sample will comprise 64 healthy patients of both genders aged from 13 to 60 with pericoronitis. After agreeing to participate, in a bio-equivalence study, participants will be evaluated in 3 different moments: baseline before PDT (T1), immediately after PDT (T2), and 4th day after PDT (T3). The clinical evaluation and the PDT treatment will be performed by the same researcher, in all 3 moments at the Dental Clinic at Nove de Julho University—UNINOVE, São Paulo, Brazil, from March, 2019 until September 2019.

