### Sample size calculation

2.1

The sample size was calculated (G∗ Power software version 3.1.9.2, Kiel, Germany) by *t* test for paired groups, since we have 2 groups (G1 conventional PS and G2 oral use PS). The effect size was determined using the formula: 

We select the worst scenario, that is, the largest standard deviation between means. The mean values of control and treated groups, as well as the standard deviation were taken from 1 study.^[18]^ The error was set at 5% and the power test at 95%. This value was calculated to provide 95% strength (α = 0.05). According to the calculus, a ample of 64 patients will be necessary to detect differences in *Tannerella forsythia* level.^[18]^ Other factors related to secondary outcomes will be analyzed statistically.

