### Statistical analysis

2.7

The data will be collected, tabulated on Excel table developed for research and presented in a descriptive way. All statistics will be conducted using the SPSS 21 program package (SPSS Inc, Chicago, IL). In the first part of the results will be performed the descriptive analysis. Measures of: absolute number, mean, standard deviation, minimum value and maximum value, percentage and cumulative percentage will be used. The bacterial count will be normalized by conversion into logarithmic values will be compared by the student *t* test. In the second part, we will verify the inferential analysis for the numerical variables. Tests of Normality Skewness and Kurtosis will be used, then verification of the homogeneity of the variables. The ANOVA will be applied for repeated data, and the Spearman correlation, and the Huynh-Feldt, Greenhouse-Geisser, Box's conservative tests. If there is no normality of the sample will be used The Wilcoxon test will be used in order to compare before and after the PDT. The *P* value is set at *P* < .05 (95% level of significance). By the end of the study, randomized groups will be revealed and statistical analysis will be performed as group A or B. The meaning of A or B will be known after statistical analysis. The data will be evaluated by comparing 2 groups: experimental and control groups (gold standard).

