## Discussion

3

The main rationale for conducting this study is to verify a possibility of treating pericoronitis with a low risk alternative. Other reasons are to suppress or reduce the quantity of antibiotics medications and to test if the new oral formulation with MB is more effective on bacterial reduction.

The primary outcome will be the presence and quantity of bacterium *T forsythia*, and secondary: pain, swelling, trismus, GCF and salivary cytokines, OHRQoL and position and classification of the lower third molars, to avoid bias the measurement of all these outcomes should be standardized.

The bacterium *T forsythia* plays an important role in the development of clinical symptoms of pericoronitis.^[28,29]^ The presence and quantity of *T forsythia* increase in 8 times the risk of developing pericoronitis, when compared to individuals without it.^[28,30,31]^ This bacterium was also associated with the development of pericoronitis in other studies and was present in 40% of their samples.^[32–35]^ Thus, it will be important to measure it properly and quantify this association.^[28]^

PDT causes non-toxic death, leading to destruction of the cell wall and consequent death of the microorganisms. The capacity of PDT to kill bacteria has been studied by several authors; Fontana et al^[16]^ found that bacteria did not reduce to the same degree as has been reported for treatment with antibiotics.

PDT is effective in destroying periodontal pathogens,^[36]^ since most oral bacteria do not absorb the visible light, it is necessary to use the PS, which must act for a period before irradiation.^[37]^

The PS binds to the cell of the microorganism because it needs to bind to negative charges and the membrane of the microorganism has more negative charge than the membrane of the host cell.^[38]^ Gram-negative bacteria induced the dye dimerization more intensely than gram-positive bacteria.^[39]^ The membrane of microorganism are always negatively charged, so the positively charges PS attach and/or aggregate to them and end up interfering on benefits of PDT process.^[40]^

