The composition of this fluid resembles that of serum, and the intensity of its flow has been shown to vary as a function of gingival inflammation. There is a wide variation in the methods of collection, storage, and analysis along with elusion protocols making the values alter based on this variation.^[54]^ Kinney et al^[23]^ concluded that the greatest degree of sensitivity was noted with GCF biomarkers compared to saliva biomarkers on the identification of periodontal disease progression, reason why it will be used this method in this study, and it will be compared to salivary cytokines.

MB was chosen as a PS. MB absorbs well the red light^[14]^ and it is the most commonly used PS in dentistry for antimicrobial action.^[6]^ The 3 minutes pre-irradiation time of MB was established based on Joseph et al^[12]^ research. Any decrease of penetration of MB in biofilm may be attributed to a reduced action of PDT,^[16]^ thus an adequate pre-irradiation time is desirable.

It is difficult to predict the efficacy of PS as many factors may contribute to their cellular photoactivity, which is usually related to properties of their monomers species.^[39]^ A decrease in photochemical effects may occur due to dimerization of MB.^[6]^ MB has a tendency to aggregate, also called metachromacy, which is the property of forming dimer or higher aggregation products upon increasing dye concentration or changing the microenvironment (e.g., high ionic strength). It interacts with the anionic macromolecule lipopolysaccharide resulting in the generation of MB dimmers.^[16]^ The absorption spectrum of MB is changed upon aggregation, altering the wavelength of highest absorption to lower wavelengths.^[11]^ Bergmann and Konski^[55]^ showed that the absorption spectrum of monomer and dimer are different. Monomer absorbs light at the wavelength of 660 nm and the dimer at 590 nm. Besides, depending on its ground state monomer/dimmer equilibrium the photochemical properties which can be shifted from type II to type I.^[10,56]^ This fact can interfere with the antimicrobial potential of PDT, since it decreases the formation of singlet oxygen.^[57]^ Here, by changing the MB vehicle, the study aims to verify if the reduced aggregation improves the antimicrobial effect.

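### The article labels the trial bioequivalence but sizes and tests it for a difference, with a superiority aim in the Discussion; the hypothesis must be reconciled

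*Protocol article*

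**What the plan says.** The protocol article takes three positions on what is being compared.

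- **Equivalence.** The abstract (Method) states: "In this randomized, controlled, double-blind clinical bioequivalence protocol, 64 healthy patients with pericoronitis will be evaluated". Section 2 (Methods) repeats the label: "After agreeing to participate, in a bio-equivalence study, participants will be evaluated in 3 different moments".
- **Difference.** Section 2.1 sizes the trial with a t "test for paired groups, since we have 2 groups (G1 conventional PS and G2 oral use PS"), at 5% error and 95% power, and concludes that a sample "of 64 patients will be necessary to detect differences in" T forsythia level. Section 2.7 says: "The bacterial count will be normalized by conversion into logarithmic values will be compared by the student" t test, with a threshold of P < .05. The control arm is described there as the gold standard.
- **Superiority.** The Discussion gives as one reason for the trial "to test if the new oral formulation with MB is more effective on bacterial reduction", and later, on the change of vehicle, says that "the study aims to verify if the reduced aggregation improves the antimicrobial effect".

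The article states no equivalence margin, no confidence-interval criterion and no two one-sided tests. It does not say how a non-significant primary result will be interpreted.

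**The concern.** In an equivalence trial the null hypothesis is that the arms differ by at least a stated margin, and rejecting it supports equivalence. In the planned t test the null hypothesis is no difference, and failing to reject it supports nothing. The label and the plan cannot both stand.

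What is at stake is the meaning of a P value above .05. Under a superiority hypothesis it is inconclusive. Under a bioequivalence label, against a control called the gold standard, it can be taken for success. The smaller or noisier the trial, the more often that result occurs, so poor precision would favour the conclusion.

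**Working it through.** **The plan's own figure.** The 64 patients of section 2.1 cannot be reproduced, because the text at hand shows no means, SD or effect size. The formula was lost in extraction, which is not counted as an error. Working backwards, 32 per arm gives 95% power at two-sided 5% for a standardised difference of about 0.92 SD, if the arms are compared as independent groups. That is a power statement about detecting a difference. An equivalence sample size cannot be computed without a margin, so section 2.1 is not an equivalence calculation under any reading.

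**Inputs.** From the article: 32 per arm (abstract, section 2.4) and the 5% level (sections 2.1 and 2.7). Assumed: an unadjusted two-sample t test between arms, all 64 evaluable, a two-sided test, and true differences and margins in SD units.

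**Precision.**
- Standard error of the difference = √(2/32) = 0.25 SD, with 62 degrees of freedom.
- 95% CI half-width = 1.999 × 0.25 = 0.50 SD.
- 90% CI half-width = 1.670 × 0.25 = 0.417 SD.

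Even if the observed difference were exactly zero, the 90% CI would run from about −0.42 to +0.42 SD.

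**Chance of P > .05 when the arms truly differ.** The noncentrality parameter is d × √(32/2) = 4d. To a close approximation the chance of a non-significant result is Φ(1.999 − 4d). For d = 0.5 this is Φ(−0.001) = 0.50. The noncentral t results are:

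| True difference (assumed) | P > .05 |
|---|---|
| 0.3 SD | 78% |
| 0.4 SD | 65% |
| 0.5 SD | 50% |
| 0.6 SD | 34% |

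**Power to show equivalence.** Take two one-sided tests, each at 5%, with truly equal arms. Power is approximately 2Φ((m − 0.417)/0.25) − 1 for margin m. For m = 0.5 this is 2Φ(0.33) − 1 = 0.26. The exact results are:

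| Margin (assumed) | Power with 32 per arm | Per arm for 95% power |
|---|---|---|
| 0.4 SD | 3% | 164 |
| 0.5 SD | 26% | 105 |
| 0.6 SD | 53% | 73 |
| 0.8 SD | 87% | 42 |
| 0.92 SD | 95% | 32 |

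The 95% power quoted in section 2.1 would therefore hold for equivalence only with a margin near 0.92 SD, given truly equal arms.

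**The case against.** The best defence is that this is a matter of labelling. The word appears twice, once in the abstract and once in passing in section 2. Section 2.4 (Design) does not use it, and the aim in the abstract and Introduction is the neutral one of evaluating effectiveness. Sizing, test and Discussion all fit a difference question, so the arms, the sample size and the test could stay as they are. That is right, and it is why the correction is cheap. It does not remove the contradiction: both uses are in the current text, and the label declares a conclusion that the analysis cannot deliver.

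A second defence is that only a condensed article is shown, so a margin may exist in the full protocol or analysis plan. That also stands in part: the supportable statement is that the article gives none. But the article itself fixes the sizing objective as a difference, and no later document can turn that into an equivalence calculation.

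Third, every effect and margin above is an assumption. Without an SD for log counts, nobody can say from these documents whether 0.8 SD is a tight or a loose margin microbiologically. The figures show scale only.

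A reader might also infer that the sponsor will report P > .05 as equivalence. The article does not say so; it is silent on how a null result will be read. The label leaves that reading open, and no more can be claimed. Nor do sections 2.1 and 2.7 already specify superiority on log10 counts at T3: they give no direction, log base or time point for the t test. Only the Discussion gives a direction.

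**Conclusion.** The point holds as a contradiction within the article about the primary hypothesis: a bioequivalence label, difference-based sizing and testing, and a superiority aim. The planned t test can serve the difference or superiority question. It cannot establish equivalence, whatever its P value.

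On the stated assumptions, a true difference of half an SD would be missed about as often as it is found, and 64 patients would give low power for equivalence at margins of 0.6 SD or less. The contradiction itself depends on none of these assumptions. It should be corrected because it decides what the primary result means, but it calls for no change to the arms, sample size or test if superiority is the intended question.

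**What to change.** 1. Delete the bioequivalence label from the abstract (Method) and section 2.
2. State the primary hypothesis as a difference between G2 and G1 in log T forsythia, with superiority of G2 as the aim, in line with the Discussion. I propose T3 as the time point, since section 2.6 gives no other post-treatment measurement of this outcome. The log base should be named.
3. In section 2.7, report the between-arm difference with its 95% CI, and state that P > .05 will not be interpreted as equivalence.

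This costs two deletions and two or three sentences.

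If equivalence is the real aim, the sponsor must instead justify a margin on the log scale, use two one-sided tests with the 90% CI, and restate the power that 64 patients give for that margin. This route may need a larger trial: under the assumptions above, 95% power takes 105 per arm for a 0.5 SD margin and 42 per arm for 0.8 SD. Either choice should be fixed before the data are analysed.

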## Introduction

1

In order to reduce the chances of systemic dissemination of the infection and the use of antibiotics, it is necessary to test effective alternative treatments in the initial phase of pericoronitis and also avoid the evolution of local infectious. Photodynamic therapy (PDT) is an interesting alternative because it is an effective antimicrobial treatment that is easy to perform and does not select bacterial resistance.^[1–3]^ The PDT also has been widely used for decontamination of endodontic channels, periodontal pockets, and reduces halitosis in adolescents, and has been considered as a noninvasive alternative and an efficient antimicrobial therapeutic method.^[3–5]^

PDT is used for decontamination, microbial reduction, in which a photosensitizer (PS) is activated by light at a specific wavelength (λ = 660 nm).^[6,7]^ The absorption of the photons by the PS, leads to a state of triple excitation of the oxygen resulting in energy or transference of the electron to the molecule of oxygen, with consequent formation of reactive species, like singlet oxygen.^[8]^

PDT relies on the appropriate combination of light, PS, and oxygen.^[9]^ Light reach the PS at the target cell in the presence of oxygen, leading to PS excitation.^[10]^ The singlet excited state PS molecules can be converted to a triplet excited state by intersystem crossing.^[2,11,12]^ The PS triplet excited state transfer energy (type II reaction) or electron (type I reaction) to the oxygen molecule, with consequent formation of singlet oxygen or free radicals, respectively.^[2,7,8,10]^ These oxidant species lead to toxic and destructive action in bacteria.^[13]^

The PS can be selectively incorporated into the bacterium.^[2,10]^ This PS selectivity may be related to time of PS action before irradiating.^[12]^ The antimicrobial effect is based on the action of the reactive oxygen species (ROS) on bacterial membrane, organelles, and DNA.^[12,10]^

Methylene blue (MB) is a phenothiazinium, cationic dye that absorbs red light.^[6]^ It is commonly used as PS for antimicrobial action at concentrations of 0.005% to 0.01%.^[12,14,15]^

Depending on the concentration, MB ground state may also work as an electric donor allowing electron transfer reactions that can either destroy PS or allow formation of other ROS, ionic strength, temperature, media, and interaction with target tissue molecules, MB can bind to other molecules forming aggregation and dimer, factor that will influence the reactions type I or type II described before.^[2,11]^ Its participation in the photosensitization process can interfere with the antimicrobial potential of PDT.^[10,16]^

PDT have additional beneficial effects at clinical and immunological aspects, because it is also responsible for photobiomodulation in tissues.^[12]^ The mechanism occurs by apoptosis, acting specifically on the mitochondria and the lysosome, since light acts improving tissue repair and decreasing the periodontal inflammatory process, that will modulate the immunoinflammatory response of the host, interfering in the levels of inflammatory cytokines.^[2,13,17]^

Due to the role of PDT and the need for new treatments for pericoronitis, the aim of this study is to evaluate the effectiveness of PDT with MB in an oral formulation in pericoronitis in the initial phase in healthy patients through microbiological, clinical, and immune response. The impact of pericoronitis on oral health-related quality of life (OHRQoL) of these patients will also be evaluated.

## Methods

2

The protocol was approved by the Research Ethics Committee of Nove de Julho University (UNINOVE), number # 2.732.106 and registered at clinicaltrials.gov NCT 03576105. The study is in accordance with the Declaration of Helsinki (revised in Fortaleza, 2013).

Participants who accept to participate will sign the Informed written Consent Form after verbal and written explanation of the study. The sample will comprise 64 healthy patients of both genders aged from 13 to 60 with pericoronitis. After agreeing to participate, in a bio-equivalence study, participants will be evaluated in 3 different moments: baseline before PDT (T1), immediately after PDT (T2), and 4th day after PDT (T3). The clinical evaluation and the PDT treatment will be performed by the same researcher, in all 3 moments at the Dental Clinic at Nove de Julho University—UNINOVE, São Paulo, Brazil, from March, 2019 until September 2019.

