### Randomization

2.3

An external researcher who will not participate in this study will perform randomization through the Microsoft Excel program, version 2013 (Microsof, Redmont, WA). To decide the type of the PS, another researcher will randomize into 4 blocks with 16 patients blocking in pairs of numbers (1:1) designed as A or B. As the study will be performed in a double-blind manner, neither the patient nor the operator will know which MB will be used as PS. To randomly distribute the treatments, the same researcher (not involved in the study) will prepare the envelopes. The letters (A or B) drawn will be placed into opaque envelopes labeled with sequential numbers. The envelopes will be sealed and remain in the same numerical order in a safe place until PDT treatment. These data will only be revealed after statistical analysis.

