### Outcome measures

2.6

All the variables (except *T forsythia* and cytokines) described below will be evaluated by the same operator at baseline, before PDT (T1), immediately after PDT (T2), and on the 4th day after PDT (T3). *T forsythia,* salivary and crevicular cytokines will be evaluated at T1 and T3.

The primary outcome will be the presence and quantity of bacterium *T forsythia.* Microbiological analysis will be performed by RT-PCR for the bacterium *T forsythia*. Biofilm samples for microbiological analysis, will be collected at 2 points of the vestibular gingival sulcus of the lower third molar using Gracey mifive curettes (Hu-Friedy, Chicago). The collected samples will be maintained in TE (Tris-EDTA), conditioned in microtubes in ice, and later transported to the laboratory analysis in the Microbiology Laboratory of ICB-USP Department of Microbiology, Institute of Biomedical Sciences for laboratory analysis. From these samples, total DNA will be extracted with Step One Plus Thermo-Time PCR System (Applied Biosystem, Foster City, CA) before amplificating them with PCR. The products will be detected by fluorescence using the Quantimix Easy SYG Kit (Biotools, Madrid, Spain), according manufacturer. For the reaction, 10 μL of SYBR Green, 0.5 μL DNA template, 200 mM of each primer corresponding to the gene (described in Table 1) will be used. Amplicons from conventional PCR will be used as quantify control curve.

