The issue of QoL has largely been neglected within the practice of oral-maxillofacial surgery.^[41]^ OHRQoL is defined as an individual's assessment of how the following elements affect well-being. Magraw et al ^[42]^ concluded that the impact of pain on patients with pericoronitis leads to a worsening OHRQoL, which can influence on the decision of third molar extraction.^[43,44]^ The OHIP-14 questionnaire asks about the adverse impacts of oral conditions on well-being.^[45]^ QoL outcomes may be as important as clinical signs when decisions are rendered regarding third molar extractions.^[26,46]^

For pain measurement, a VAS will be included as the main instrument for assessing the patients’ complaint regarding pain. It is graduated in centimeters, which allows the use of parametric tests, which improves accuracy of data analysis.^[28,47,48]^ Pain affects most domains of QoL,^[49]^ which depends on the extent, duration, acuteness, intensity, affectivity, and meaning of the pain, as well as the underlying disease and the individual's characteristics.^[26]^

In order to avoid bias, and to try to eliminate subjectivity factors of pain and quality of life, the same researcher will measure all outcomes and they should be standardized using established methods as VAS and OHIP-14.

Classifications are used to predict the surgical degree of difficulty, and to evaluate the risk of pre and postoperative complications.^[25]^ Pell and Gregory and Winter techniques,^[26]^ are the most common techniques to evaluate tooth position. It evaluates the tooth depth position in the vertical direction (relative to the occlusal plane and in relation to the neck of the adjacent second molar) and horizontally (as it evaluates the position of the tooth in relation to the ramus of the mandible). In order to classify the position of a tooth, the position of the teeth will be evaluated through panoramic radiography, according to the classification of Pell and Gregory and Winter ^[26]^ performed only by 1 evaluator, following the criteria of imaginary lines as proposed by Almendros-Marques et al.^[27]^

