Another researcher will apply the red diode laser. The red light will act to improve tissue repair and decrease the periodontal inflammatory process, especially on facial swelling and trismus ^[22]^ and also will modulate the immunoinflammatory response of the host, interfering in the levels of inflammatory cytokines. Corrêa et al,^[13]^ Candeo et al,^[9]^ and Kellesarian et al^[17]^ found a reduction of the pro-inflammatory cytokines IL1-β, IL-6, IL-8, and TNF-α after the PDT. So we will try to verify if PDT will promote advantageous modulation of cytokine levels in pericoronitis.

Macrophages that are frequently found in pericoronitis are able to produce the wide range of pro-inflammatory and anti-inflammatory mediators, as well as substances that enhance pro and anti-inflammatory substances. These substances act in the development and repair of these lesions, expressing IL-1α, TNF-α, IL-6, TGF-β, and prostaglandins and cytokines that act at the beginning and regulation of inflammatory processes through the activation and differentiation of osteoclasts, activation and proliferation of fibroblasts, production of collagen and neovascularization.^[50]^ Tumor necrosis factor (TNFα) is a cell signaling protein (cytokine) involved in systemic inflammation and is one of the cytokines that make up the acute phase reaction.^[51]^ It is produced chiefly by activated macrophages, although it can be produced by many other cell types. IL1-β, IL-6, and IL-8 are interleukins that act as pro-inflammatory cytokines. IL-10 is an anti-inflammatory cytokine.

The GCF is a transudate of interstitial tissues which is produced by an osmotic gradient, and it is released into the crevicular sulcus. However, during periodontal inflammation, the main mechanism of GCF formation becomes exudative, with an increase in its flow rate, and thus volume.^[52]^ Cytokines produced by various cells are strong local mediators of inflammation.^[53]^ GCF, an exudates, harnessed from the sulcus or periodontal pocket, has been regarded as a promising medium for the detection of periodontal disease activity.^[54]^ GCF has also demonstrated a potential value to evaluate periodontal therapy efficacy.^[23]^

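### The article contradicts itself on whether the outcome assessor also gives PDT, and a fixed A/B code with ambiguous block wording makes masking fragile if that person sees the letters

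*Protocol article*

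**What the plan says.** **Who treats and who assesses.** The opening of section 2 (Methods) gives both tasks to one person: "The clinical evaluation and the PDT treatment will be performed by the same researcher, in all 3 moments". Section 2.6 (Outcome measures) says that the variables other than *T forsythia* and cytokines, as it puts it, "described below will be evaluated by the same operator at baseline", and at the two later time points. Section 2.5 also uses the word operator for the person at the laser. The Discussion first says that "the same researcher will measure all outcomes", offered as a way of avoiding bias, and shortly afterwards: "Another researcher will apply the red diode laser".

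**Masking.** Section 2.3 (Randomization) says that "neither the patient nor the operator will know which MB will be used as PS". Someone outside the study prepares sealed envelopes: "The letters (A or B) drawn will be placed into opaque envelopes labeled with sequential numbers". They are kept in a safe place until treatment. Section 2.7 keeps A and B as the analysis groups and discloses their meaning only after the analysis.

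**Blocks.** Section 2.3 describes four blocks of 16 patients and, in the same sentence, "blocking in pairs of numbers (1:1) designed as A or B".

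**Products.** Section 2.5 describes both as a blue solution, 0.4 mL at 0.005%. The Objective in the abstract places the test product in an astringent vehicle.

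**The concern.** This is a conflict between statements in the text, not a detail left to a fuller protocol. Under the Methods wording, the person who places the solution in the gingival sulcus and hears the patient's remarks then takes the caliper measurements and gives the VAS instructions. Under the Discussion wording, someone else handles at least the laser.

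The difference matters because the arms differ only in the methylene blue formulation. Masking therefore depends on the vehicle difference going unnoticed, and the person who applies the product is well placed to notice it. A single assessor improves consistency of measurement, but it does not protect masking if that assessor also treats.

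The allocation code adds to this. Two letters fixed for the whole trial mean that one recognised product carries over to other patients with the same letter. If the effective block size is 2, someone who sees the letters can also predict many of them. That could influence the order of enrolment once a person believes they know what a letter stands for.

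**Working it through.** **1. The role statements side by side**

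| Place | Gives PDT | Assesses outcomes |
|---|---|---|
| Section 2, opening | same researcher as the assessor | same researcher as the treater |
| Section 2.5 | operator | not addressed |
| Section 2.6 | not addressed | same operator throughout (not PCR or cytokines) |
| Discussion | another researcher (laser) | same researcher for all outcomes |

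Sections 2, 2.5 and 2.6 point to one person in both roles. Only the Discussion separates them. Read in its natural sense, the Discussion cannot hold together with the opening of section 2.

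**2. What must happen for the assessor to be unmasked through the code**

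(a) The assessor applies or sees the product. (b) The assessor recognises one product from its vehicle. (c) The assessor sees patients' letters. The opening of section 2 would supply (a). The article establishes neither (b) nor (c). If all three held, the product would be identified for every patient whose letter was seen, and for no others by this route.

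**3. How predictable the letters are**

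Inputs from section 2.3: 4 blocks × 16 = 64, which agrees with the stated sample size; allocation 1:1. Effective block size is either 2 or 16. Assumption: a person sees all earlier letters and knows the block size.

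Take a permuted block of size 2h with h of each letter. A letter is determined once all remaining letters in its block are the same. The expected number determined per block is 2h/(h + 1).

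- Block of 2 (h = 1): 2 × 1/2 = 1 per block; 32 blocks give 32 of 64 = 50%.
- Block of 16 (h = 8): 2 × 8/9 = 1.78 per block; 4 blocks give 7.1 of 64 = 11.1%.

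Exact enumeration, guessing at each step the letter with more left in the block, gives the expected share guessed correctly:

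| Scheme | Letters determined | Guessed correctly |
|---|---|---|
| Blocks of 2 | 32 of 64 (50%) | 48 of 64 (75%) |
| Blocks of 16 | 7.1 of 64 (11.1%) | 40.2 of 64 (62.8%) |
| No blocking | 0 | 50% |

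These figures concern letters, not products.

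**4. Which outcomes are exposed**

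*T forsythia* (primary) and the cytokines are laboratory assays. Pain is marked by the patient on the VAS, and OHIP-14 consists of the patient's own answers. Swelling and mouth opening are read from a caliper by the assessor. The direct exposure is therefore those two secondary measures. Indirect influence is possible on the instructions for the VAS and OHIP-14, and on biofilm and fluid sampling if the same person collects the samples.

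**The case against.** The strongest reply has four parts.

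First, the contradiction may be only apparent. The Discussion's sentence about another researcher comes just after a statement on the single evaluator of the radiographs, so it might mean someone other than that evaluator. This is possible. But the Discussion has already given all outcomes to one researcher, and tooth position is listed among the outcomes, so the more natural reading is someone other than the assessor. The wording needs settling in either case.

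Second, a reader might infer that the assessor's blinding is easily lost, or that one recognised product unmasks all 64 patients. The article supports neither. It states that patient and operator are masked, uses sealed opaque envelopes prepared outside the study, and describes both products as a blue solution. A predicted letter reveals nothing until the product behind it is recognised, and all 64 patients would be affected only if all 64 letters were seen. Who opens the envelopes, who fills the syringe and whether the products are matched may be given in a full protocol; their absence from an article is no fault. This part stands, and it makes the masking concern conditional.

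Third, pairs may only describe balanced numbering within blocks of 16. That reading is open, so the 50% figure cannot be stated as a fact about the trial.

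Fourth, the primary outcome is laboratory PCR, and pain and quality of life are reported by the patient. This also stands, and it limits what is at stake.

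**Conclusion.** The point holds in a limited form. The statements on who treats and who assesses conflict and must be reconciled. The block wording permits two schemes that differ materially in predictability: 50% or 11% of letters determined for someone who sees the earlier ones.

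Masking is fragile, not shown to be broken. That judgement rests on three assumptions: the assessor also applies the product, the letters are visible to that person, and the vehicle can be recognised in use. The first follows from the Methods wording; the other two are not stated either way. Loss of masking would bear directly on swelling and mouth opening, both secondary, and at most indirectly on the patient-reported scales and on sampling. The laboratory reading of the primary outcome is not exposed. The change is worth making because it is cheap and removes a dependence on nobody noticing a vehicle difference.

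**What to change.** 1. Reconcile the opening of section 2 and section 2.6 with the Discussion. State that the researcher mentioned there carries out the whole treatment step, solution and laser, and that the outcome assessor is absent from it and returns for the measurements that follow. The Discussion gives that researcher only the laser, so adding the solution is a new assignment that must be written down.
2. Have the external researcher supply syringes labelled with the patient number only, so that no A or B letter is seen in clinic. That researcher keeps the link between numbers and letters, and the analysis under masked labels in section 2.7 is unaffected. This breaks the carry-over from one patient to the next. It does not stop a treater or patient from noticing a perceptible vehicle, which is why step 1 is also needed.
3. Replace the wording on pairs in section 2.3 with one unambiguous block scheme, preferably of varying sizes that are not disclosed to clinic staff.

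Cost: 64 labelled syringes, a new allocation list, and two researchers present at the treatment visit, both already mentioned in the article. No change to sample size, outcomes or visits is needed.
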